## Abstract

Possible sarcopenia refers to low muscle strength. Prevalence of possible sarcopenia is estimated to be significantly higher in community-dwelling older adults than that of confirmed or severe sarcopenia. However, there are currently far fewer non-pharmacological intervention strategies for possible sarcopenia than for sarcopenia in the community. Meanwhile, one type of non-pharmacological intervention in sarcopenic area, health education, is under-researched, and older people’s awareness about sarcopenia is extremely low, necessitating an immediate dissemination tool for prevention. Social media may be a potential, scalable, low-cost tool for this. This study protocol outlines how a social media-based multicomponent intervention will be co-designed with stakeholders to address this evidence gap. Guided by the Medical Research Council’s framework, the proposed research covers two phases that employ a co-design approach to develop a theory-based multicomponent intervention to increase sarcopenia prevention in the community. The participants will be recruited from young-old adults (60~69) with possible sarcopenia in the community of Changsha, China. Maximum sample size will be 45 participants in total, with 18~25 participants in the development phase and 15~20 participants in the pre-test phase. During two rounds of focus groups with older adults, a social-media based intervention strategy will be developed from a theory-based conceptual model and an initial intervention plan formulated by the research group. After this, there will be a three-week pre-test phase, followed by a semi-structured interview to further modify the theory-based conceptual model and the social-media based intervention strategy. The focus of the data analysis will be on thematic analysis of qualitative data primarily derived from the group interview and the semi-structured interview with key stakeholders.

## Introduction

Possible or probable sarcopenia refers to low muscle strength, which is a relatively new classification proposed by the European Working Group on Sarcopenia in Older People (EWGSOP2, 2018) [1] and the Asian Working Group for Sarcopenia (AWGS, 2019) [2]. The prevalence of possible sarcopenia is quite high among community-dwelling older adults. According to a latest population-based longitudinal study conducted in China, the estimated prevalence of older adults aged 60 years and over with possible sarcopenia in the community was 46.0% [3]. Pérez-Sousa et al. [4] investigated 5237 Colombian older adults aged≥60 years and found that the prevalence of probable sarcopenia was as high as 46.5%. Several recent cross-sectional studies also reported a high prevalence of possible sarcopenia in older population living in the community, with 26.9% in Swiss (>60y) [5], 25.4% in Greek (≥75y) [6], 23.7% in Korean (≥65y) [7]. Besides, Wu et al. [8] discovered that the prevalence of possible sarcopenia (38.5%) among Chinese older people in the community was significantly higher than that of confirmed (18.6%) and severe (8.0%) sarcopenia.

The young-old age group has a high prevalence of possible sarcopenia, but relatively fewer intervention methods, requiring additional focus. Up to 71% of the participants in the longitudinal study conducted in China who reported possible sarcopenia were between 60 and 70 years of age [3]. More than half (52%) of the older Colombians diagnosed with possible sarcopenia in the cross-sectional study were aged 60 to 69 years [4]. Wu et al. [9] examined that the prevalence of possible sarcopenia among adults aged 55 years and older at 11 rural community daycare centres in Taiwan was as high as 68.7%. In addition, our recent scoping review about the non-pharmacological interventions for possible sarcopenia or sarcopenia revealed that 70-79-year-olds (64.8%) have been studied more than 60-69-year-olds (18.5%) in community-dwelling older adults, and the number of interventions for possible sarcopenia (11.9%) was significantly lower than for sarcopenia (72.9%) [10]. However, both the EWGSOP2 and AWGS2019 recommend possible sarcopenia as an important threshold to trigger assessment of causes and initiate intervention in medical practice [1,2].

Non-pharmacological interventions are essencial for sarcopenia prevention, but health education is under-researched and public awareness about sarcopenia is extremely low. Health Education, as defined by the World Health Organization, refers to the deliberate creation of learning opportunities that involve communication aimed at enhancing health literacy. This includes improving knowledge and developing life skills that promote individual and community health [11]. A cross-sectional study examined the current knowledge of middle-aged and older adults in Netherlands regarding sarcopenia and showed that only 9% of participants (57.0~75.1y) reported knowing what sarcopenia is [12]. EWGSOP2, AWGS2019, and some researchers recommend facilitating timely lifestyle interventions and related health education for primary health care in community and prevention settings, which will increase awareness of sarcopenia prevention and intervention in diverse health care settings [1,2,13–15]. Nevertheless, our scoping review found that there were 142 intervention groups designed in 59 studies for preventing possible sarcopenia or sarcopenia in the community, but the proportion of intervention groups containing health education components (15.5%) was substantially lower than those containing exercise or nutrition components (52.8% and 34.5%, respectively) [10]. In 22 intervention groups containing health education components, up to 18 groups (81.8%) provided education materials unrelated to sarcopenia, which may be the primary reason for unsatisfactory results of existing health education [10]. Furthermore, this scoping review identified only three traditional forms of health education, including group-based classes, face-to-face interactions and leaflets/materials [10], which appears to be significantly fewer than the forms of health education in other chronic diseases, like digital health education on diabetes management [16] and social media as an educational platform on hypertension [17–19]. An integrative review indicated that technologies promoting health education for older adults in the community also included software, videos, mock-up and so on [20].

In the context of an Internet era and in light of the increased use of digital tools during the covid-19 pandemic, social media may be a promising medium for health education to disseminate knowledge and raise awareness of disease prevention among older adults. For instance, a pilot study in United States demonstrated that a social media-based (WeChat) health education was feasible, acceptable, and potentially efficacious in self-management education of older adults with type 2 diabetes [21]. Another qualitative research found that a photography-based, social media (Facebook) walking game was well received by older women and also benefited for increasing their motivation for physical activity, fostering a shift in perspective, increasing their knowledge, and providing health-related benefits to them [22]. TikTok, a platform for sharing short videos, has been phenomenal since the onset of the COVID-19 pandemic and has reached Chinese seniors [23] by providing simple video-editing tools [24] and catering to specific informational and practical needs [25,26]. A qualitative research showed that during the COVID-19 pandemic, WeChat and TikTok played a significant role in providing older Chinese adults with access to valuable health information; and many older adults were able to modify their health behaviours after incorporating this information and knowledge into their daily lives [27]. Kassamali et al. [28] reported that TikTok held great potential as a platform for disseminating educational information about disease, as their study indicated that the number of views for the hashtag such as #acne, #alopecia, #cyst, #rosacea, and #psoriasis on TikTok doubled in just 5 months. Nonetheless, there are currently no studies utilizing social media for sarcopenia prevention. Hence, TikTok may be a valuable platform for attempting to develop a short-video-based intervention strategy to prevent sarcopenia in Chinese older adults.

This research programme was founded on behaviour change theories. Previous researches have already demonstrated that exercise could improve sarcopenic indices in sarcopenia patients [29–31], but the maintenance of improvements in long-term behaviour change in community-dwelling older adults with sarcopenia is unclear [10]. Strong evidence indicates that successful behaviour change interventions in physical activity include several key components, such as theoretical framework, useful intervention components, and behaviour change techniques [32–35]. Therefore, this study constructed a new conceptual model primarily guided by Michie et al.’s Behaviour Change Wheel (BCW) [32] and the conceptual model for Lifestyle- integrated Functional Exercise using smartphones and smartwatches (eLiFE) [33], with the objective of developing intervention content and monitoring process. BCW is a framework (S1 Fig) [32] mainly for developing intervention content for behaviour change, and several studies have demonstrated its efficacy and recommended its use in interventions for older adults [36,37]. In addition, the intervention phase was derived from the eLiFE conceptual model (S2 Fig) [33], which assists older adults in forming long-term physical activity habits through the use of a mobile app, and the eLiFE programme was shown to be feasible and safe for young seniors [38]. We integrated the BCW and eLiFE conceptual models to create a new SHEEP conceptual model for preventing sarcopenia among older people (Fig 1).

**Fig 1 pone.0286490.g001:**
[figure not shown]
SHEEP conceptual model. This is the initial version of the model, which was plan to undergo further modification as the research advances. The complete designations of the abbreviations in this model are as follows: C-Ps, psychological capability; C-Ph, physical capability; M-Re, reflective motivation; M-Au, automatic motivation; O-Ph, physical opportunity; O-So, social opportunity.

To improve the acceptability of the theory-based intervention strategy among older individuals, co-design method will be employed. Strong evidence found that patients (even those close to death) and their families were consistently willing to engage in research [39]. Co-design in health care services typically refers to active collaboration between researchers, specialists, health care professionals, and non-academic partners such as patients or family members who are regarded as ‘experts of their experiences’ [40–42]. In recent years, co-design methods have been utilised extensively in health care interventions, for example, a co-designed mHealth programme to promote healthy lifestyles [43], a co-designed intervention to improve communication about the heart failure trajectory [44], and co-designing complex interventions with people living with dementia and their carers [45]. Whether it is used for research or service improvement, co-design has been proved to be beneficial for study projects, users and services [40,43–48]. There is currently no evidence of co-design in the field of sarcopenia research, making the exploration of this study particularly valuable.

### Study aims and objectives

The overall aim of this research is to develop a theory-based and social-media based intervention for preventing possible sarcopenia through behaviour change in community-dwelling young-older adults. More specifically, the main objectives are: 1) To co-design a multicomponent intervention (health education plus exercise) strategy based on the SHEEP Conceptual Model; 2) To conduct a pre-test stage to refine both the intervention strategy and the SHEEP Conceptual Model. Thus, the following research questions will be posed: 1) What intervention contents should be included in different part of health education and exercise training? 2) How to ensure the correct dose of health education and exercise (in terms of frequency, intensity, and duration) can be achieved using a social-media based approach?

## Materials and methods

### Study design

The SHEEP programme was structured under the guidance of the UK Medical Research Council (MRC) for developing and evaluating complex interventions [49]. This research protocol outlined the initial stage (intervention development) in the MRC’s guidance. Co-design method is the most crucial technique for completing the formulation of a social-media based intervention strategy to prevent sarcopenia among targeted population in this project. According to the five guiding principles and systematic framework proposed by Leask et al. [50] for designing, implementing, and evaluating co-designed public health interventions, consideration is given to first completing the designing phase in this study, in order to formulate a social-media based intervention strategy that incorporates the perspectives of the relevant stakeholders. This includes the preparing, developing, and pre-test phases (Fig 2).

**Fig 2 pone.0286490.g002:**
[figure not shown]
Flow chart of this research protocol. The study encompasses three main phases: preparation, development, and pre-test, which was plan to be completed during January to August, 2023.

· Preparing: In January and February of 2023, the research team developed an initial intervention plan based on literature reviews, the SHEEP Conceptual Model, and consultations with specialists regarding health education and exercise contents, frequency, intensity, and duration.

· Developing: Between March and June of 2023, there were two rounds of focus groups in the development procedure. Each round included three focus groups, to which older adults with possible sarcopenia were invited. The aim of the first round of focus groups was to discuss the initial intervention plan’s flaws with participants and adapt it to the needs of the target population; we then created short videos based on the revised plan. The purpose of the second round of focus groups was to modify the content of each short video further.

· Pre-test: During July and August of 2023, a pre-test process was conducted with the goal of refining the SHEEP conceptual model and optimising the social-media-based intervention strategy and intervention process.

### Research setting

The entire study will be conducted at the Community Nursing Department of Xiang Ya Nursing School, Central South University, or within their cooperative community in Changsha, Human Province, China. It should be noted that the recruitment process will take place in a location that participants prefer based on their individual needs, such as the home of older participants or an office provided by our collaborator at Xiang Ya Nursing School or in the community. In addition, the co-design process will take place in an office provided by Xiang Ya Nursing School or the community, depending on the preference of the majority of participants within each focus group. However, if face-to-face focus groups are prohibited by local policy due to an outbreak, we will switch to online focus groups using Tencent Conference Software.

### Research participants

Although different scholars interpreted the definition of "young-old" differently, such as 60–69 years or 65–74 years [51,52], based on the fact that this study will be conducted in China, 60–69 years is considered young-old for the purposes of this study. Participants must satisfy the following inclusion criteria: (1) 60~69 years old; (2) Chinese residing in the community; (3) using TikTok prior to recruitment; (4) individuals with possible sarcopenia, as defined by low Grip Strength [M:<28 kg, F:<18kg] [2], which will be measured with a digital handheld dynamometer (EH101, Xiangshan Inc, Guangdong, China); (5) informed consent to screening and research. The following are the criteria for exclusion: (1) unable to communicate or independently complete learning on TikTok in Chinese; (2) with serious or unstable medical illness, such as severe cardiovascular or respiratory conditions, mental disorder, dementia, etc.; (3) sufficient physical activity (≥ 150mins/week) [53,54].

### Sampling method and sample size

Purposive sampling will be used to select relevant stakeholders. To avoid bias against subgroups, we will select older adults based on their gender (male and female) and age (60~65y and 66~69y). We aim to recruit a maximum sample of 45 older adults in total. For developing phase, 18~25 older adults will be recruited to participate in focus groups (with a 10~15% attrition rate), and then invited to take part in both the first and the second round of focus groups. Each round will consist of three focus groups, with 18~25 participants divided into three groups of at least six members each, which is based on the recommendations of Leask et al. [50] that 10~12 co-creators in total is advised in co-design research and the Guidelines for Conducting a Focus Group that suggests six to ten people will be appropriate for a focus group [55]. Besides, we require 15~20 additional participants for the pre-test phase. In the two phases of our study, participants have the option of participating in only focus groups, only pre-test, or both focus groups and pre-test.

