Using topic guides, at least two rounds of focus groups comprised of older adults with possible sarcopenia will be conducted (Fig 3). There will be at least six older adults in each focus group during each round. The optimal time allotted for each focus group is 45 to 90 minutes, during which no more than twelve predetermined questions are discussed [55]. If face-to-face focus groups are prohibited by local epidemic policy, we will consider conducting online focus groups instead. The purpose of the first round of focus groups is to discuss the problems in the paper version of the initial intervention plan and modify it based on the suggestions of our participants to better fit the targeted population. Following this, we will create short videos based on the revised paper plan. The short videos will include two categories of short instructional videos for TikTok: health education and exercise (Fig 4). Then, the second round of focus groups will seek to modify the content of each short video further. If there are numerous issues with short videos, we will consider conducting a third round of focus groups to review all of the revised short videos and ensure that each segment is appropriate for our stakeholders and free of controversy.

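### The lower recruitment bound of 18 leaves no margin for the stated 10–15% attrition, so three focus groups of six are not expected in both rounds unless about 20–22 people are recruited (minor)

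*Protocol article*

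**What the plan says.** All the figures are in the Protocol article.

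- **Number recruited and expected loss** (Sampling method and sample size): "18~25 older adults will be recruited to participate in focus groups (with a 10~15% attrition rate").
- **One cohort for both rounds** (same section): the recruits are "and then invited to take part in both the first and the second round of focus groups".
- **Groups and minimum size** (same section): "Each round will consist of three focus groups, with 18~25 participants divided into three groups of at least six members each".
- **The minimum applies in every round** (Development phase): "There will be at least six older adults in each focus group during each round".
- **Ceilings** (Sampling method and sample size): "We aim to recruit a maximum sample of 45 older adults in total", and for the later phase "Besides, we require 15~20 additional participants for the pre-test phase".

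The article states no rule for replacing people who drop out and no smaller permitted group size. Recruitment, consent and withdrawal allows participants to leave at any time without giving a reason.

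**The concern.** The range 18–25 is used twice: once for the people recruited, and once for the people divided into groups in each round. With 10–15% attrition and no replacement, one range cannot describe both. The conflict matters at the lower end, because 18 is the product of three groups and six members, with nothing added for loss.

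What is at stake is the group size that the design promises. A team that recruits 18 is within the plan, yet on the plan's own attrition figure it should expect about five people per group by the second round. The focus groups are the main source of data for developing the intervention, and the second round is where participants comment on the individual videos.

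**Working it through.** **Inputs**, all from Sampling method and sample size, with the minimum repeated in Development phase:
- recruits N = 18 to 25
- attrition d = 10% to 15%
- three groups per round, each with six or more members
- the same people in rounds 1 and 2

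**Step 1. Reproduce the lower bound.** Attendees needed per round = 3 × 6 = 18. This equals the stated lower bound with d = 0.

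**Step 2. Expected number remaining, N × (1 − d), and the same divided by three.**

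| Recruited | Left at 10% (per group) | Left at 15% (per group) | Reaches 18? |
|---|---|---|---|
| 18 | 16.2 (5.4) | 15.3 (5.1) | at neither rate |
| 19 | 17.1 (5.7) | 16.15 (5.38) | at neither rate |
| 20 | 18.0 (6.0) | 17.0 (5.67) | at 10% only |
| 21 | 18.9 (6.3) | 17.85 (5.95) | at 10% only |
| 22 | 19.8 (6.6) | 18.7 (6.23) | at both |
| 25 | 22.5 (7.5) | 21.25 (7.08) | at both |

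**Step 3. Recruits needed, 18 / (1 − d), rounded up.**
- At 10%: 18 / 0.90 = 20.
- At 15%: 18 / 0.85 = 21.18, so 22.

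The cruder inflation 18 × (1 + d) gives 19.8 and 20.7, so 20 and 21. Neither method gives 18.

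**Step 4. Chance that at least 18 remain.** This treats losses as independent between people, which is an assumption of this review and not of the protocol.

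| Recruited | 10% attrition | 15% attrition |
|---|---|---|
| 18 | 0.150 | 0.054 |
| 20 | 0.677 | 0.405 |
| 22 | 0.938 | 0.774 |
| 25 | 0.998 | 0.975 |

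**Step 5. Could 18–25 be the number left after attrition?** The overall maximum is 45 = 25 + 20, so 25 counts recruits. If 25 were the number left, recruitment would be 25 / 0.90 = 27.8 (28) to 25 / 0.85 = 29.4 (30). The total would then be 28 + 20 = 48 to 30 + 20 = 50, above 45.

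**The case against.** The strongest defence is that 18 is meant as the attendance floor and the upper part of the range is the attrition allowance: 22 recruits cover 15% loss, and 22 lies inside 25. The intention may well have been this. It does not rescue the wording, because the text gives 18 as a number recruited and nothing requires recruitment of 22 or more. The plan is met with 18 to 21.

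A second defence is that losses may fall only between rounds, so that round 1 still has 18. That is possible, but the minimum is stated for each round, and round 2 would then have about 15–16.

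Three stronger readings are tempting, and the documents do not support them:

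- *That recruiting 18 makes the design impossible.* It makes the minimum unlikely to be met. If nobody drops out, 18 is enough.
- *That the videos are settled in round 2, so thin groups there would do lasting harm.* Development phase allows a third round to review revised videos, and Pre-test phase provides further testing and modification, repeated if its pass criterion is missed.
- *That this is a serious flaw.* The main analysis is thematic, no power calculation depends on the group size, and Discussion says that no conclusions about effectiveness will be drawn. The 15–16 people left would still exceed the 10–12 co-creators that the article cites.

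It is also fair to say that 22 meets the minimum only in expectation. At 15% loss the chance of keeping 18 is 0.774 under the independence assumption.

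**Conclusion.** The point holds as a minor internal inconsistency. On the article's own figures, the lower recruitment bound carries no allowance for the attrition stated beside it. The expected shortfall at 18 recruits is 1.8 people at 10% attrition (18 − 16.2) and 2.7 at 15% (18 − 15.3). The range 18–19 is too low in expectation at both rates and 20–21 at 15%; 22–25 is adequate.

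This rests on three readings of the text: that 18–25 counts recruits, that the attrition applies to people attending by round 2, and that dropouts are not replaced. The expectation needs no independence assumption; only the probabilities do.

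**What to change.** In Sampling method and sample size:

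1. Restate the developing-phase recruitment range as 22–25. Use 20 as the lower bound only if 10% attrition is assumed.
2. Give 18 as the minimum number attending in each round (three groups of six), separately from the number recruited.

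The ceilings stay as they are: 25 for this phase and 25 + 20 = 45 overall. The cost is a change of wording and up to four more recruits than the current lower bound (22 − 18). A team that wants more than expected adequacy can aim for the top of the range, where 25 recruits keep at least 18 with probability 0.975 at 15% loss, under independence.

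The outline of phases under Study design describes the focus groups in the past tense (March to June 2023), while other sections use the future tense. If the groups have already been held, a new target changes nothing in conduct. In that case, correct the text and report the actual attendance for each group and round.
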